#### Other study parameters

In order to take account of possible confounding variables, other parameters are: age, gender, marital status, socio-economic status, smoking history, condition of living (single, or living together), and place of living (home, residential home, or nursing home).

### Randomization

Randomization will not take place. Hospitals will be selected for the intervention condition based on the presence of a specialized palliative care team in the hospital. In order to be able to compare the hospitals in the control- and the intervention condition a pre-test assessment will be performed.

### Study procedure

A description of the procedure is given to assess the defined study parameters.

#### Pre-test assessment

The following data on hospital level will be obtained from the databases of the participating hospitals retrospectively over a period of one year (1-1-2013 till 1-1-2014):

● Number of hospitalizations for AECOPD (including ICU admissions)

● Number of unique patients hospitalized for AECOPD (including ICU admissions)

● Total number of days of hospitalization of patients with an AECOPD (including ICU admissions)

● Number of hospitalizations in the ICU (exclusively) for AECOPD

● Number of unique patients hospitalized for AECOPD in the ICU (exclusively)

● Total number of days of hospitalization of patients with an AECOPD in the ICU (exclusively)

● Total number of patients hospitalized for AECOPD that have died in the hospital (in the ICU or on the nursing unit)

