### Study design

The study consists of a controlled trial (assessment) with hospital as cluster, with a pre- and a post-test assessment. In total 6 hospitals will participate, 3 hospitals in the intervention condition and 3 hospitals in the control condition. Hospitals are selected for the intervention condition based on the presence of a specialized palliative care team. In the hospitals in the control condition standard care (usual care) will be delivered to patients with COPD by their treating lung specialists. In the hospitals in the intervention condition all patients with COPD will receive standard care by their treating lung specialist and those patients that are indicated for proactive palliative care by our set of indicators will also be supported by a specialized palliative care team on a regular base. Baseline measurements of the intervention study will be assessed from all participating patients during hospitalization for AECOPD before start of the intervention. Follow-up measurements will take place every three months, starting from the moment of discharge for a period of one year or until death. The primary outcome measure of the indicator study is time to death for any cause. The primary outcome measure of the intervention study is the change in quality of life measured by the St George Respiratory Questionnaire (SGRQ) at three month after baseline. As pre-test assessment, data will be obtained from the databases of the participating hospitals over a one year period preceding the assessment. These data on hospital-level are necessary to be able to compare hospitals at baseline. As post-test assessment, retrospectively the medical files of all participating patients will be examined over the assessment period. The assessment will take 18 month; 6 month for inclusion and 12 months for follow-up. The post-test assessment will be performed in the 3 months after the assessment.

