##### Lung specialist

The treating lung specialist will provide standard care (usual care) to the patients hospitalized for an AECOPD. After the patient has filled out and returned the questionnaires the lung specialist in the control- and the intervention condition will fill out a case report form (CRF). The CRF consists of questions about the measurement results of each indicator of the set of indicators. The set of indicators is represented in Table 1. Only in the intervention condition the lung specialist will check if a patient meets two or more criteria of the set of indicators for proactive palliative care.

**Table 1 T1:** Set of indicators for proactive palliative care

**A patient hospitalized for AECOPD is eligible for proactive palliative care when meeting two or more criteria of the following set of indicators:**	
1.	Hypoxaemia or hypercapnia at discharge
2.	Treatment of the exacerbation with Non Invasive Ventilation (NIV)
3.	Patient needs professional home care service for personal care after discharge
4.	Negative answer to the surprise question: ‘Would I (as lung specialist) be surprised if this patient would have a subsequent readmission for AECOPD within 8 weeks and/or would die in the next year?
5.	The diagnosis of a severe comorbidity such as:
	a. Non-curable malignity or
	b. Cor pulmonale (proven or non proven) or
	c. Proven Chronic Heart Failure (CHF) or
	d. Diabetes mellitus with neuropathy or
	e. Renal failure, clearance < 40 (GFR: in ml/min)
6.	CCQ total, day version ≥ 3
7.	MRC dyspnea = 5
8.	FEV1 (measured before AECOPD) < 30% of predicted
9.	BMI < 21 or unplanned weight loss (> 10% weight loss in last 6 months or > 5% in last month)
10.	Previous hospital admissions for AECOPD (last 2 years ≥ 2 and/or last year ≥ 1)
11.	Age > 70 years

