#### Post-test assessment

A post-test assessment will be performed in all participating hospitals. The medical files of all participating patients will be examined retrospectively regarding the assessment period on the following measures:

● Number and length of hospitalization of unexpected hospital admissions for AECOPD

● Number and length of hospitalization of unexpected ICU admissions for AECOPD

● Are the choices of Advance Care Planning (ACP) documented in the medical file? (when yes/when no)

● Place of death (ICU/hospital/hospice/nursing/home/at home)

● Is preferred place of death known? (when yes/when no)

● Has this wish come true? (when yes/when no)

● Length of survival after meeting conditions for proactive palliative care

● The primary and secondary measures of the indicator study

In order to take account of possible confounding variables, other parameters are: age, gender, marital status, type of admission, (acute or planned), condition of living (single, or living together), place of living (home, residential home, or nursing home), Gold stage, comorbidities, and date of diagnosis.

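### The pre-test yields hospital totals only and prior admission days and ICU use are not collected per participant, so the secondary admission outcomes cannot be properly adjusted for earlier use

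*Protocol article*

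**What the plan says.** The Study design section describes the trial thus: "The study consists of a controlled trial (assessment) with hospital as cluster, with a pre- and a post-test assessment". Under Randomization and again in the Discussion, the protocol article explains that hospitals enter the intervention condition because they have a specialized palliative care team, and that a pre-test is done so that the two sets of hospitals can be compared.

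The pre-test is introduced with "The following data on hospital level will be obtained from the databases of the participating hospitals retrospectively over a period of one year" and covers calendar year 2013. Its items are totals, among them "Number of hospitalizations for AECOPD (including ICU admissions" and "Total number of days of hospitalization of patients with an AECOPD (including ICU admissions", with matching ICU items and a count of in-hospital deaths.

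The post-test works on other material: "The medical files of all participating patients will be examined retrospectively regarding the assessment period on the following measures". The first measure listed is "Number and length of hospitalization of unexpected hospital admissions for AECOPD", followed by its ICU counterpart. These supply secondary outcomes 2e and 2f of the intervention study.

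Confounders are listed twice, under Other study parameters and under Post-test assessment. Together the lists cover demographic and social items, smoking, type of admission, Gold stage, comorbidities and date of diagnosis. Admission history appears only as indicator 10 in Table 1: "Previous hospital admissions for AECOPD (last 2 years ≥ 2 and/or last year ≥ 1".

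**The concern.** When hospitals are chosen for a feature of their organization, their patients may differ in how often they were admitted before the trial, and the hospitals may differ in how readily they admit patients or use the ICU. The protocol itself treats earlier admissions as prognostic: the Background says that exacerbations cluster in time and become more frequent as the disease advances, and previous admissions are one of the eleven indicators.

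A difference between conditions in prior use would therefore be expected to carry over into admissions during follow-up, whatever the palliative care team does. The remedy offered for the lack of randomization is the pre-test, so it matters whether the pre-test, or anything else collected, allows that difference to be taken out of outcomes 2e and 2f. Fewer and shorter acute and ICU admissions are among the stated hypotheses, and the Discussion refers to reduced acute care when it argues that costs may be saved.

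**Working it through.** No figure in the plan bears on this point, so the check sets the sections side by side.

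**Step 1. Can the pre-test data serve as a baseline covariate for 2e and 2f?**

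| | Pre-test assessment | Post-test assessment |
|---|---|---|
| Unit | hospital total | individual patient |
| Source | hospital database | patient's medical file |
| Population | everyone admitted with an exacerbation | consenting participants |
| Event | any exacerbation admission | unexpected ones only |
| Period | 2013 | assessment period |

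The pre-test gives one value per hospital and item, six values in all. Every patient in a hospital shares that value, so it carries no information on differences between patients. With three hospitals per condition and condition fixed by hospital, a hospital-level covariate leaves very little to estimate from. It also describes all inpatients, not the participants being compared. The pre-test can describe; it cannot adjust.

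**Step 2. Does another listed item do the job?**

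- Confounder lists (Other study parameters; Post-test assessment): neither contains prior admissions, prior days or prior ICU use.
- File review: confined to the assessment period, which Study design sets at 18 months (6 for inclusion, 12 for follow-up). Even read as one calendar window for every patient, it would reach back between 0 and 6 months before inclusion, depending on when the patient entered. It would not give a common 12-month history.
- Indicator 10: the lung specialist completes the case report form in both conditions, with the results for each indicator. Some history on the number of admissions therefore exists. As printed, the indicator is a threshold, with no days and no ICU component.
- Selecting patients with at least two of the eleven indicators does not equalize prior admissions. A patient can qualify with or without indicator 10.

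**Step 3. What analysis is stated?** The section on the intervention study names Fisher's exact, chi-square and independent-samples t-tests for differences in baseline characteristics and clinical outcomes. Adjustment is stated for SGRQ over follow-up (baseline score) and for survival (demographic characteristics). None is stated for admissions.

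**Step 4. Size.** To first order, the bias in the difference in mean admissions equals the difference between conditions in mean prior admissions, multiplied by the increase in follow-up admissions per prior admission. The article gives neither quantity, so no value or sign can be put on it.

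**The case against.** A reader might infer from the pre- and post-test label that a change in admissions was intended and that the data make it impossible to compute. The documents do not support that. Study design, Randomization and Discussion give the purpose of the pre-test as comparing hospitals at baseline. The outcome list words quality of life, psychological wellbeing and caregiver burden as changes, but 2e and 2f as numbers and lengths. No change score is promised, so its absence is no fault.

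The pre-test also serves its stated purpose. Its items yield admissions per unique patient, days per admission, ICU share and in-hospital deaths for each hospital before the trial. A reader might go further and ask for the database query to be repeated in the trial period, with the item "Total number of patients hospitalized for AECOPD that have died in the hospital (in the ICU or on the nursing unit" split by ICU and ward. That is not needed. About 29 qualifying patients per hospital would be diluted in a hospital-wide total, and place of death is already recorded per participant.

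The strongest remaining objection is that adjustment belongs in an analysis plan that is not shown, and that the case report form may record admission counts rather than a yes or no. Both may be true, and the choice of model can be left to that plan. But the article fixes what is extracted from the files and for which period. A later plan cannot adjust for prior days or ICU admissions that were not collected.

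**Conclusion.** The point holds in a limited form. As listed, the data allow hospitals to be described before the trial, but they do not allow the participant-level comparison of unexpected admissions and ICU admissions to be adjusted for earlier use, beyond what indicator 10 offers. The stated group tests would carry any difference in prior use between the selected hospitals into outcomes 2e and 2f.

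The size is unknown. Any figure would rest on assumed admission rates, so none is given. The conclusion assumes only that prior use may differ between hospitals chosen in this way and that it predicts later use; the protocol takes the second as given when it makes previous admissions an indicator. The point concerns secondary outcomes only, since SGRQ has its own baseline measurement in each patient. The lack of randomization is disclosed and explained, and is not itself the fault.

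**What to change.** In the post-test file review, also extract for every participant, over the 12 months before the index admission:

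1. number of exacerbation admissions,
2. days in hospital for them,
3. number of ICU admissions for exacerbation,
4. days in the ICU for them.

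Add these to the confounder list under Post-test assessment, and state that outcomes 2e and 2f are compared with adjustment for them. The entry for indicator 10 on the case report form can be used to cross-check the first field. Keep the pre-test as a description of the hospitals.

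Cost: four fields per patient from files that are opened anyway. With the planned 60 to 90 participants in each of six hospitals (360 to 540 patients), that is 4 × 360 = 1,440 to 4 × 540 = 2,160 entries. If limited to the qualifying patients (2 × 86 = 172), it is 4 × 172 = 688. The work is retrospective and changes neither recruitment nor care. Two limits remain: admissions to other hospitals may be missed, and adjustment for prior use does not remove other differences between the two sets of hospitals.

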#### Training

Before start of the controlled trial (see Figure 2), members of the specialized palliative care teams in the hospitals in the intervention condition will receive a special training in provision of proactive palliative care for patients with COPD.

**Figure 2 F2:**
[figure not shown]
Study schema of the controlled trial (assessment) and the post-test assessment for PROLONG.

#### Controlled trial (assessment)

##### Patient

Patients in the control condition will receive standard care (usual care) only. Patients in the intervention condition will receive standard care and, only if they meet two or more criteria of the set of indicators for proactive palliative care they will receive proactive palliative care integrated with standard care. The procedure in the control condition will be first described before describing the procedure in the intervention condition.

In the hospitals in the control condition eligible patients will be recruited the second day after hospital admission. The treating lung specialist will give each eligible patient oral and written information about the study. The written information consists of an information leaflet and two informed consent forms: one for the patient and one for the informal caregiver. In the information leaflet a description of the study, including the nature of participation and phone numbers for study contacts, are given for the patient and the informal caregiver. The lung specialist will obtain written informed consent from the patient prior to enrollment. If a patient has consented, a lung nurse will distribute questionnaires for completion on the sixth day of hospital stay or in case the patient is discharged earlier on the day before leaving the clinic. After hospital discharge the patient will be asked by the study coordinator to complete questionnaires every 3 month until the end of the study or until death. The questionnaires will be sent to the patient by mail. A stamped retour envelope will be enclosed.

In the hospitals in the intervention condition the same procedure will be followed as in the hospitals in the control condition. In addition lung specialists will check if a patient meets two or more criteria of the set of indicators for proactive palliative care on the sixth day of hospital admission or in case the patient is discharged earlier on the day before leaving the clinic. If so, the lung specialist will inform the specialized palliative care team. Patients who are assigned for proactive palliative care will preferably meet for the first time with a physician of the specialized palliative care team before being dismissed from the hospital. If this is not possible the first meeting will take place within 1 week after enrolment. Thereafter, the specialized palliative care team will meet with the patient monthly in the outpatients setting for at least 1 year or until death.

##### Informal caregiver

During hospital stay, each eligible patient will identify a main informal caregiver, a relative or friend whom he or she relies upon most for help. By sharing the written information with the informal caregiver, the patient will provide the informal caregiver with information about the study. The informal caregiver can only participate if the patient is also participating. Once the informal caregiver has consented questionnaires will be distributed during hospital stay and every 3 month after hospital discharge of the patient. These questionnaires will be sent in the same envelop as the patient questionnaires.

##### Lung specialist

The treating lung specialist will provide standard care (usual care) to the patients hospitalized for an AECOPD. After the patient has filled out and returned the questionnaires the lung specialist in the control- and the intervention condition will fill out a case report form (CRF). The CRF consists of questions about the measurement results of each indicator of the set of indicators. The set of indicators is represented in Table 1. Only in the intervention condition the lung specialist will check if a patient meets two or more criteria of the set of indicators for proactive palliative care.

**Table 1 T1:** Set of indicators for proactive palliative care

**A patient hospitalized for AECOPD is eligible for proactive palliative care when meeting two or more criteria of the following set of indicators:**	
1.	Hypoxaemia or hypercapnia at discharge
2.	Treatment of the exacerbation with Non Invasive Ventilation (NIV)
3.	Patient needs professional home care service for personal care after discharge
4.	Negative answer to the surprise question: ‘Would I (as lung specialist) be surprised if this patient would have a subsequent readmission for AECOPD within 8 weeks and/or would die in the next year?
5.	The diagnosis of a severe comorbidity such as:
	a. Non-curable malignity or
	b. Cor pulmonale (proven or non proven) or
	c. Proven Chronic Heart Failure (CHF) or
	d. Diabetes mellitus with neuropathy or
	e. Renal failure, clearance < 40 (GFR: in ml/min)
6.	CCQ total, day version ≥ 3
7.	MRC dyspnea = 5
8.	FEV1 (measured before AECOPD) < 30% of predicted
9.	BMI < 21 or unplanned weight loss (> 10% weight loss in last 6 months or > 5% in last month)
10.	Previous hospital admissions for AECOPD (last 2 years ≥ 2 and/or last year ≥ 1)
11.	Age > 70 years

##### Specialized palliative care team

The specialized palliative care teams in the hospitals in the intervention condition consist of specially trained teams of professionals who provide care and support in inpatient and outpatient settings. A team consists of at least a physician who is specialized in palliative care, a nurse who is specialized in palliative care, and preferably a psychologist and a spiritual counselor.

#### Post-test assessment

A post-test assessment will be performed in all participating hospitals. The medical files of all participating patients will be examined retrospectively regarding the assessment period on the following measures:

● Number and length of hospitalization of unexpected hospital admissions for AECOPD

● Number and length of hospitalization of unexpected ICU admissions for AECOPD

● Are the choices of Advance Care Planning (ACP) documented in the medical file? (when yes/when no)

● Place of death (ICU/hospital/hospice/nursing/home/at home)

● Is preferred place of death known? (when yes/when no)

● Has this wish come true? (when yes/when no)

● Length of survival after meeting conditions for proactive palliative care

● The primary and secondary measures of the indicator study

In order to take account of possible confounding variables, other parameters are: age, gender, marital status, type of admission, (acute or planned), condition of living (single, or living together), place of living (home, residential home, or nursing home), Gold stage, comorbidities, and date of diagnosis.

### Tools to help the clinical decision making

In order to help the clinical decision making, the specialized palliative care team will make use of two additional tools: 1) the Problems and Needs in Palliative Care questionnaire short version (PNPC-sv) and 2) the Proactive Palliative Care Planning Card (PPCPC).

The PNPC-sv patient is a concise, patient-centered tool that helps to identify the problems affecting the patient’s quality of life and (unmet) needs for care. This self-report questionnaire is covering all dimensions of palliative care. The questionnaire consists of 36 items and is a reliable and valid tool [40].

The PPCPC is a tool that can be used by members of the specialized palliative care team to structure the discussion with the patient and his/her informal caregiver. This tool is especially useful when exploring the actual en potential problems and needs of the patient [41].

### Data collection

Data collection will take place by administration of questionnaires to the participating patients and their informal caregivers and by retrospectively collecting data from the medical files of the participating patients over the assessment period. The type of questionnaires for patients and informal caregivers, the frequency of their administration and the retrospectively collected data are detailed in Table 2.

**Table 2 T2:** Overview of outcome measures per time point in the PROLONG study

**Outcome measures**	**B**	**3 m**	**6 m**	**9 m**	**12 m**	**R**

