**Medical files**						
Number of hospitalisations of unexpected hospital admissions for AECOPD						X
Number of days of unexpected hospital admissions for AECOPD						X
Number of hospitalisations of unexpected ICU admissions for AECOPD						X
Number of days of unexpected ICU admissions for AECOPD						X
Are the choices of ACP documented in the medical file at baseline? (when yes/when no)						X
Are the choices of ACP documented in the medical file after one year or at time of death? (when yes/when no)						X
Did the patient die within one year after inclusion? (when yes/when no)						X
Date of death						X
Place of death (ICU/hospital/hospice/nursing home/at home)						X
Is preferred place of death known? (when yes/when no)						X
Has this wish come true? (when yes/when no)						X
Primary cause of death (pulmonary insufficiency/other cause)						X
Secondary cause of death (pulmonary insufficiency/other cause)						X
Did the patient have an unexpected hospital readmission for AECOPD within 8 weeks? (when yes/when no)						X
Date of first unexpected hospital readmission for AECOPD.						X

B = baseline; m = month; R = retrospectively.

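### Deaths are ascertained only from medical files in the participating hospitals, while scheduled monthly contact until death exists only for flagged intervention patients, so capture of out-of-hospital deaths can differ by arm.

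*Protocol article*

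**What the plan says.** The Data collection section names two sources: questionnaires to patients and informal caregivers, and file review, described as "by retrospectively collecting data from the medical files of the participating patients over the assessment period". Table 2 divides the items between them. Under its Medical files heading, marked only in the retrospective column, are "Did the patient die within one year after inclusion? (when yes/when no", date of death, "Place of death (ICU/hospital/hospice/nursing home/at home", "Primary cause of death (pulmonary insufficiency/other cause" and secondary cause of death. None of the questionnaires in Table 2 is marked as a source for a death item.

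The Post-test assessment section places this work in the hospitals: "A post-test assessment will be performed in all participating hospitals". It covers both arms: "The medical files of all participating patients will be examined retrospectively".

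Contact during follow-up is described under Controlled trial (assessment), Patient. In the intervention hospitals, for patients meeting two or more indicators, "the specialized palliative care team will meet with the patient monthly in the outpatients setting for at least 1 year or until death". Control patients receive usual care. In both conditions the study coordinator mails questionnaires every three months until the end of the study or death, with the caregiver's forms in the same envelope (Informal caregiver section).

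**The concern.** The place-of-death categories show that the study expects deaths at home, in a hospice or in a nursing home. A file held in a hospital need not record such a death, or its date, place and cause, unless someone reports it. A team that meets the patient monthly until death, with the caregiver invited, is a likely route for that report. Control patients have no equivalent scheduled contact. The intervention itself may thus change the chance that a death reaches the only stated source.

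Three sets of results use these data:
- Time to death from any cause is the primary outcome of the indicator study.
- Survival is the secondary objective of the intervention study, analysed by Kaplan-Meier and Cox models.
- Place of death is a secondary outcome of the intervention study.

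The primary outcome of the intervention study, SGRQ change at three months, does not use this source.

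**Working it through.** The plan states no capture rate, mortality or place-of-death distribution, so there is no figure of its own to reproduce. The calculation below is a sensitivity range on assumed inputs.

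**Assumptions.** True hazard ratio 1; one-year mortality m = 25% in both arms; share of deaths outside hospital o = 50%; in-hospital deaths always captured; no deaths missed in the intervention arm; a fraction q of out-of-hospital deaths missed in controls and counted as survivors.

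**Formulas.**
- Recorded control mortality: m_C = m(1 − o·q)
- Apparent hazard ratio, intervention versus control: ln(1 − m) / ln(1 − m_C)
- Apparent in-hospital share of control deaths: m(1 − o) / m_C

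**Results.** The out-of-hospital deaths amount to 0.25 × 0.50 = 12.5% of patients.

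| q | Missed | Recorded control mortality | Apparent HR | In-hospital share, controls (true 50%) |
|---|---|---|---|---|
| 0 | 0% | 25.0% | 1.00 | 50% |
| 10% | 1.25% | 23.75% | ln 0.75 / ln 0.7625 = 1.06 | 12.5/23.75 = 53% |
| 20% | 2.5% | 22.5% | ln 0.75 / ln 0.775 = 1.13 | 12.5/22.5 = 56% |
| 40% | 5.0% | 20.0% | ln 0.75 / ln 0.80 = 1.29 | 12.5/20 = 63% |

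With 86 patients per arm (Sample size calculation), q = 20% and 40% correspond to about 86 × 0.025 = 2.2 and 86 × 0.05 = 4.3 missed control deaths.

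**Wider grid.** Mortality was varied from 20% to 40% and the out-of-hospital share from 30% to 70%. Capture of out-of-hospital deaths (intervention versus control) was set at 100% vs 90%, 95% vs 80% and 95% vs 60%. The apparent hazard ratio then runs from 1.03 to 1.44. With equal capture (100% or 95% in both arms) it is 1.00 in every scenario.

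**Direction.** Missed control deaths make control survival look better, which works against the intervention. The same omissions leave the recorded control deaths too concentrated in hospital, which works in favour of the intervention on place of death.

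**Indicator study.** Let D_F and D_U be the true deaths in flagged and unflagged patients, captured with probabilities c_F and c_U. Measured sensitivity is c_F·D_F / (c_F·D_F + c_U·D_U). It is unchanged if c_F = c_U, too high if c_F > c_U, and too low if c_F < c_U. In intervention hospitals the flagged patients have the extra contact, which points to c_F > c_U there. In control hospitals neither group has it. The documents do not fix the net direction.

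**The case against.** The strongest reply is that the same file review is applied to every participant in every hospital, and that out-of-hospital places are listed as values to be read from the file, so the authors expect the file to hold them. The coordinator's mailing reaches both arms and stops at death, which suggests that the coordinator learns of deaths. Participating caregivers are contacted in both arms. Controls remain under their lung specialist. How vital status is verified and how unknown status is handled may be set out in the full protocol or analysis plan, which are not shown.

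Much of this stands as a limit on the claim. A reader might infer that deaths are in fact recorded differently by arm and that the results are biased. The documents do not support that: they give no capture rate, and with equal capture there is no between-arm bias in the hazard ratio. That the files are the hospital's own is a strong inference from the Post-test assessment section, not its wording. The extra contact belongs only to flagged intervention patients. A reader might also infer that missed deaths must lower the indicator set's measured discrimination; the algebra above shows that they could equally raise it. Nor does the article say that a patient without a recorded death is counted as alive.

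The size is also modest beside sampling error. With 86 × 0.25 = 21.5 expected deaths per arm, the standard error of the log hazard ratio is about √(2/21.5) = 0.30, so apparent ratios of 1.13 and 1.29 represent roughly 0.4 and 0.8 standard errors.

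The reply does not remove the point. The source of the death data is stated item by item, so it is a design choice and not a detail left out. Table 2 does not draw on the mailing for any death item, and the article does not say that a non-returned questionnaire prompts a check of vital status. The restriction to flagged patients does not weaken the arm comparison, because the intervention study is aimed at, and sized on, patients with a poor prognosis.

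**Conclusion.** The concern holds as a risk built into the stated data source. Death items rest on file review alone, and scheduled contact until death differs by arm and, within intervention hospitals, by indicator status. If capture of out-of-hospital deaths follows contact, survival is biased against the intervention and place of death in its favour. The effect on the indicator study's discrimination has no determinable direction.

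The size is unknown. Under the main assumptions, with 0–40% of out-of-hospital deaths missed in controls only, the spurious hazard ratio lies between 1.00 and about 1.29, and the in-hospital share of control deaths reads between 50% and 63% against a true 50%. Every input to that range except the 86 patients per arm is assumed. The change is worth making because the risk is avoidable and cheap to remove, not because bias has been shown.

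**What to change.** In the three-month post-test period, confirm 12-month vital status for every participant at all six hospitals and, for deaths, the date, place and cause. Use one procedure that does not depend on arm or indicator status: a query to the GP or to the informal caregiver, whose name the patient's demographic questionnaire already collects. State this source in Data collection and Table 2 alongside the medical file.

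Censor patients whose status cannot be confirmed at last known contact instead of counting them as alive. Report their number by arm and indicator status; censoring is a fallback and does not replace near-complete confirmation, since unconfirmed patients may be those who died.

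The cost is one short query per patient by the study coordinator and a line in the information leaflet and consent form. No visit or procedure is added.
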